## 1.2 CANDIDATE SPECIFIC TRIAL SCHEMA

[figure not shown]

### 1.3 SCHEDULE OF OBSERVATIONS AND PROCEDURES (Phase I and II)

|                                                       | Screening k | Day 1
(baseline) | Daily
whilst in hospital
(days 2-14) | Specific Assessments on
Days 3, 5, 8, 11 (±1 days) | Day 15
(±2 days) | Day 29
(±2 days) |
|-------------------------------------------------------|------------------------|---------------------|--------------------------------------------|-------------------------------------------------------|---------------------|---------------------|
| Informed consent                                      | X                      |                     |                                            |                                                       |                     |                     |
| Check Eligibility                                     | X a         | X                   |                                            |                                                       |                     |                     |
| Randomisation                                         |                        | X                   |                                            |                                                       |                     |                     |
| Telephone Contact b (AEs, Con-Meds)        |                        |                     | Daily apart from in hospital               |                                                       |                     |                     |
| Demographics                                          | X                      |                     |                                            |                                                       |                     |                     |
| Treatment compliance - up to day 7                    |                        |                     | X (Day 2 to 7)                             |                                                       |                     |                     |
| AE/SAE assessment                                     | X (from consent)       | X                   | X                                          | X                                                     | X                   | X                   |
| 12 lead ECG i                              | X                      |                     |                                            |                                                       |                     |                     |
| SARS-CoV-2 surveillance NP swab                       |                        | X                   | Daily for 1 st 5 days           | X                                                     | X                   | X                   |
| SARS-CoV-2 translational NP swab                      |                        | X                   |                                            | X c                                        |                     |                     |
| Full Blood Count                                      | X d         | X                   | As per SoC                                 | X                                                     | X                   | X                   |
| U&Es                                                  | X d         | X                   | As per SoC                                 | X                                                     | X                   | X                   |
| Uric acid                                             | X d         | X                   | As per SoC                                 | X                                                     | X                   | X                   |
| Estimated GFR                                         | X d         | X                   | As per SoC                                 | X                                                     | X                   | X                   |
| LFTs                                                  | X d         | X                   | As per SoC                                 | X                                                     | X                   | X                   |
| PK assessment (Plasma, dried blood spots)             |                        | X e      |                                            | X e                                        |                     |                     |
| PK assessment (tears, saliva, nasal secretions, PBMC) |                        | X fg     |                                            | X fg                                       |                     |                     |
| Pregnancy test WOCBP                                  | X (serum)              |                     |                                            |                                                       |                     | X (urine)           |
| Urinary analysis                                      | X d         | X                   |                                            |                                                       |                     | X                   |
| Medical history (including COVID-19 history)          | X                      |                     |                                            |                                                       |                     |                     |
| Con-med/SoC review                                    | X                      | X                   | X                                          | X                                                     | X                   | X                   |

|                                                                        | Screening k  | Day 1
(baseline) | Daily
whilst in hospital
(days 2-14) | Specific Assessments on
Days 3, 5, 8, 11 (±1 days) | Day 15
(±2 days) | Day 29
(±2 days) |
|------------------------------------------------------------------------|-------------------------|---------------------|--------------------------------------------|-------------------------------------------------------|---------------------|---------------------|
| Height/Supine length/Weight l                               | X                       |                     |                                            |                                                       |                     |                     |
| WHO Progression scale                                                  | X                       | X                   |                                            | X                                                     | X                   | X                   |
| Vital signs j (NEWS2, HR, BP, RR, sats & temp)              | X                       | X                   | X                                          | X                                                     | X                   | X                   |
| Assessment of oxygen use (low flow, high flow, mechanical ventilation) | X h          | X h      | X h                             |                                                       | X (if hospitalised) |                     |
| Targeted physical exam                                                 | X                       | X                   | X                                          | X                                                     | X                   | X                   |
| Chest X-ray/other chest imaging                                        | If clinically indicated |                     |                                            |                                                       |                     |                     |
| Blood collection for translational research                            |                         | X
(pre dose)     |                                            | X                                                     | X                   | X                   |
| End of study                                                           |                         |                     |                                            |                                                       |                     | X                   |

a. Can be conducted on Day 1 but must be prior to randomisation to confirm eligibility

b. Additional week 24 telephone consultation for pregnancy follow up if female participants became pregnant.

c. Day 3 and 5 only.

d. Results are required prior to dosing only if clinically indicated

e. PK sampling for Phase I: Day 1 (pre-dose, 0-1 hr, 2-4 hr and 6-12 hr post completion of first infusion), Day 3 (pre-dose, 0-1 hr, 2-4 hr and 6-12 hr post completion of first infusion) and at Day 5 (0-1 hr and 6-12 hr post completion of the first infusion). **NOTE:** 6-12 hours post infusion must be taken prior to second infusion

f. Non-plasma PK sampling for Phase I: tears, saliva, nasal collections Day 1 and Day 3 (6-12 hours post completion of infusion)

g. Intracellular (PBM) sampling for Phase I: Day 1 and Day 3 (6-12 hr post completion of first infusion) and at Day 5 (6-12 hr post completion of the first infusion)

h. If supplemental oxygen not being administered, lowest oxygen saturation over the last 24 hours to be recorded as part of baseline/screening

i. 12-lead ECG and 10 second ECG rhythm strip (≥5 min supine), to be performed during screening, or on baseline day 1 prior to first dose

j. Vital signs on Day 1 are collected prior to dose administration (as per AGILE CST6 Acceptable Time Windows Working Instruction)

k. Screening and Day 1 can occur on the same day, therefore if not already done at screening, perform all screening procedures at baseline if on the same day, if not, then repeat on baseline as per SoA.

l Height and weight may be taken from current admission

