### Clinical studies

In total 33 phase I studies have been conducted in the US or Japan during which the safety profile appeared similar to that of placebo and comparator agents with the exception of asymptomatic elevations in uric acid levels. Elevations in blood uric acid trended towards baseline or within normal ranges after Favipiravir study dosing completed and, therefore, were not considered clinically significant. No other clinically notable shifts in serum chemistry, hematology/coagulation, urinalysis, or other special laboratory parameters were observed. To date, Favipiravir has not been shown to have any clinically significant effect on QT prolongation, or in special populations such as the elderly or patients with renal impairment. Dosage adjustment of Favipiravir should be considered for patients with hepatic impairment.

Three phase II studies in patients with uncomplicated influenza have been completed with favipiravir's safety profile similar to that of placebo with the exception of asymptomatic elevations in uric acid. Four phase III studies in patients with uncomplicated influenza have been completed. As was noted in earlier phase studies, Favipiravir administration was associated with asymptomatic elevations in uric acid. Uric acid elevations were noted at Day 5 and resolved or trended towards baseline by the first post-dosing assessment time point on Day 15. At baseline, the mean uric acid level for the Favipiravir group was 0.263 mmol/L for females and 0.342 mmol/L for males. At Day 5, the mean uric acid level for the Favipiravir group was 0.417 mmol/L for females and 0.448 mmol/L for males. At Day 15 (the first post-treatment time point analyzed), the mean uric acid level had fallen to 0.288 mmol/L for females and 0.368 mmol/L for males. The elevations in uric acid were not associated with any clinically identifiable AE known to be associated with acute or chronic elevations of uric acid (e.g. gout, urate nephropathy). Such AEs are known to develop after notably higher uric acid elevations over considerably longer periods of time.

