## 5.2 EXCLUSION CRITERIA

The main trial exclusion criteria are outlined in the master protocol as:

1. Alanine aminotransferase (ALT) and/or aspartate aminotransferase (AST)  $> 5$  times the upper limit of normal (ULN)
2. Stage 4 severe chronic kidney disease or requiring dialysis (i.e., estimated glomerular filtration (eGFR) rate  $< 30$  mL/min/1.73 m^2)
3. Pregnant or breast feeding
4. Anticipated transfer to another hospital which is not a study site within 72 hours
5. Known Allergy to any study medication
6. Patients taking the following prohibited drugs within 30 days or 5 times the half-life (whichever is longer) of enrolment:

There are no known prohibited drugs with Favipiravir.

The following drugs should be used with caution when given with Favipiravir (Liverpool, n.d.):

- Pyrazinamide: Pyrazinamide administration with favipiravir examined possible renal urate transporter interactions. Pyrazinamide increased blood uric acid levels 2 to 9 mg/dL over baseline. The addition of favipiravir increased blood uric acid levels 4 to 11 mg/dL over baseline, indicating a moderate additive effect.
- Repaglinide: Favipiravir administration with repaglinide, an anti-diabetic agent that is extensively metabolized by CYP2C8 and CYP3A4, increased repaglinide plasma AUC 30 to 50% due to inhibition of CYP2C8.

- Theophylline: Theophylline administration with favipiravir increases plasma Cmax and AUC of favipiravir through xanthine oxidase (XO) interaction. The primary metabolite of theophylline is known to be metabolized by XO which is partially involved in metabolism of favipiravir.
  - Famciclovir, Sulindac: Famciclovir and Sulindac are converted to active metabolite by Aldehyde Oxidase (AO). Favipiravir inhibits AO and decrease the concentration of active metabolite of Famciclovir and Sulindac.
  - Paracetamol: Coadministration of paracetamol (650 mg once daily) and favipiravir (1200 mg twice daily or 800 mg twice daily) increased paracetamol Cmax and AUC by 3% and 16% (1200 mg doses) and by 8% and 14% (800 mg doses). The daily dose of paracetamol in adults should be no more than 3000 mg/day (rather than 4000 mg/day).
7. Patients participating in another clinical trial of an investigational medicinal product (CTIMP) and actively taking CTIMP within 30 days

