### 5.5 REGISTRATION / RANDOMISATION PROCEDURES

Patients are registered on the trial database following consent. Randomisation is performed within the trial database when patients have completed screening and eligibility has been confirmed.

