### **8.2.1 Baseline Visit (Day 1, day of randomisation)**

The following assessments are to be carried out on the day of randomisation. Patients should commence treatment on the day of randomisation (i.e. Day 1).

- Assessment using the WHO Clinical Progression Scale (WHO, 2020):
  0. Uninfected, no viral RNA detected
  1. Ambulatory mild disease, asymptomatic; viral RNA detected
  2. Ambulatory mild disease, symptomatic; independent
  3. Ambulatory mild disease, symptomatic; assistance needed
  4. Hospitalised moderate disease, no oxygen therapy (If hospitalised for isolation only, record stats as for ambulatory patient)
  5. Hospitalised moderate disease, oxygen by mask or nasal prongs
  6. Hospitalised severe disease, oxygen by NIV or high flow
  7. Hospitalised severe disease, intubation and mechanical ventilation  $pO_2/FiO_2 \geq 150$  or  $SpO_2/FiO_2 \geq 200$
  8. Hospitalised severe disease, mechanical ventilation  $pO_2/FiO_2 < 150$  ( $SpO_2/FiO_2 < 200$ ) or vasopressors
  9. Hospitalised severe disease, mechanical ventilation  $pO_2/FiO_2 < 150$  and vasopressors, dialysis, or ECMO
  10. Dead
- Non-Ventilated Patients: National Early Warning Score 2 (NEWS2) Assessment:
  - Respiration rate
  - Oxygen saturation
  - Systolic blood pressure
  - Pulse rate
  - Level of consciousness or new confusion\*
  - Temperature

\*The patient has new-onset confusion, disorientation and/or agitation, where previously their mental state was normal – this may be subtle. The patient may respond to questions coherently, but there is some confusion, disorientation and/or agitation. This would score 3 or 4 on the GCS (rather than the normal 5 for verbal response), and scores 3 on the NEWS system.

Vital Signs are collected prior to dose administration, + 30 minutes, end of infusion +1 hour post infusion for Dose 1 only.

- Concomitant medication and standard of care review
- Assessment of oxygen use (low flow, high flow)
- Assessment of mechanical ventilation use ((Only if supplemental oxygen not being administered, lowest oxygen saturation over the last 24 hours to be recorded as part of baseline/screening))
- Adverse event assessment
- SARS-CoV-2 nose/throat swab for storage for future translational research
- SARS-CoV-2 surveillance NP swab

- Chest X-Ray (if clinically indicated)

In addition, for candidate specific trial protocol the following are required:

- Review inclusion and exclusion criteria and confirm eligibility
- Randomisation

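### The protocol contradicts itself on whether liver and kidney results must be known before a patient is randomised and dosed

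*Protocol*

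**What the plan says.** **The waiver.** In the schedule of observations (protocol section 1.3), footnote d is attached to the Screening cells for full blood count, U&Es, uric acid, eGFR, LFTs and urinalysis. It reads: "Results are required prior to dosing only if clinically indicated". The Day 1 cells in those rows carry no footnote. Section 8.2.1 uses the same wording in another place: there it applies to baseline bloods that are taken because none were done within 24 hours of baseline.

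**The criteria that need the results.** Section 5.2 excludes patients whose ALT and/or AST exceeds 5 times the upper limit of normal (criterion 1). It also excludes those with "Stage 4 severe chronic kidney disease or requiring dialysis", which it spells out as an eGFR below 30 mL/min/1.73 m² (criterion 2).

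**The eligibility rule.** Section 5.5 states: "Randomisation is performed within the trial database when patients have completed screening and eligibility has been confirmed". Footnote a of the schedule says of the eligibility check: "Can be conducted on Day 1 but must be prior to randomisation to confirm eligibility". Section 8.2.1 lists a review of the inclusion and exclusion criteria on Day 1, alongside randomisation.

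**The timing.** Section 8.1 allows screening up to 1 day before randomisation, and footnote k allows screening and Day 1 to be the same day. Section 8.2.1 has treatment start on the day of randomisation.

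**The concern.** Two of the exclusion criteria are laboratory thresholds, and the schedule tells sites that the tests measuring them need not be back before the first infusion unless there is a clinical reason. Other parts of the protocol tell sites to confirm eligibility before randomising. A site cannot confirm that ALT, AST and eGFR lie on the right side of a threshold without having a value.

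Two sites could therefore follow different parts of the protocol, both believe themselves compliant, and enrol different populations. Some patients whom the protocol means to exclude could receive the drug. For the liver criterion the protocol gives its own reason for care: "Dosage adjustment of Favipiravir should be considered for patients with hepatic impairment" (section 2.2, Clinical studies).

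Such patients would also enter the analysis. Section 10.3.1 counts as evaluable every Phase I patient randomised to favipiravir who has had at least one dose. Section 10.3.2 defines the Phase II efficacy population as everyone randomised.

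**Working it through.** No power, error rate or sample size is involved, so there is nothing to recompute. The check is whether the instructions can all be followed at once.

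| Place in protocol | What it requires |
|---|---|
| 1.3, footnote d (Screening LFT and eGFR cells) | Results needed before dosing only where clinically indicated |
| 8.2.1, baseline bloods bullet | Same waiver, for bloods not done within 24 hours of baseline |
| 5.2, criterion 1 | ALT and/or AST must not exceed 5 times the upper limit of normal |
| 5.2, criterion 2 | eGFR must not be below 30 mL/min/1.73 m² |
| 1.3, footnote a | Eligibility check completed before randomisation |
| 5.5 | Screening complete and eligibility confirmed before randomisation |
| 8.2.1, Day 1 list | Criteria reviewed and eligibility confirmed on Day 1 |
| 1.3, footnote k | Screening and Day 1 may coincide |

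1. **Order of events.** Under footnote a and section 5.5, eligibility is confirmed before randomisation. Allocation must be known before favipiravir or placebo can be given, so randomisation precedes dosing.
2. **Consequence of the waiver.** If a result is not needed before dosing, it is not needed before randomisation, which is earlier still.
3. **Consequence of the eligibility rule.** If section 5.5 and footnote a require ALT, AST and eGFR to be known, those results are always needed before dosing. Footnote d then has no effect for LFTs and eGFR.
4. **Result.** Either footnote d is empty for these two rows, or it lets the eligibility check go ahead without the values. The protocol does not say which is meant, and no passage limits footnote d or ranks it against section 5.5.
5. **Does an earlier sample always resolve it?** No. With same-day screening, the sample covered by the waiver may be the only study sample taken before the first dose. Section 5.2 names no other source and no time window for ALT, AST or eGFR.
6. **Do the two placements of the waiver agree?** No. The schedule puts it on screening bloods and leaves Day 1 unmarked. Section 8.2.1 puts it on baseline bloods, and the list of screening tests in section 8.1 carries no waiver.

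The screening serum pregnancy test, which informs exclusion criterion 3, carries no footnote d. So the waiver is not applied to every screening test that bears on eligibility. It covers a routine panel in which LFTs and eGFR sit beside tests, such as uric acid, that decide no criterion.

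**The case against.** **The protocol never permits enrolment of excluded patients.** A reader might infer from footnote d that excluded patients may be dosed. The text does not support that. Footnote d speaks of the timing of results and waives no criterion, and three places require eligibility before randomisation. A site that randomised with unknown ALT or eGFR would arguably breach section 5.5. This stands: the defect is a contradiction that leaves a route open, and that route is opposed elsewhere in the protocol.

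**A narrower reading is possible.** In section 8.2.1 the waiver covers Day 1 bloods. Where screening results already exist, that conflicts with nothing, and the footnote in the schedule may simply be in the wrong column. This is plausible, but it does not cover same-day screening, and as printed the footnote is on the screening cells.

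**Other information may identify these patients.** Medical history, recent routine bloods, or the clinical-indication clause itself would catch some of them, particularly those with known kidney disease or on dialysis. This also stands, although the protocol does not say that such sources suffice. It is one reason why no count is offered. The documents give neither the share of screened in-patients meeting criteria 1 or 2 nor the share who would be missed. Any Phase II count would also have to separate the up to 99 patients on favipiravir from the up to 99 on placebo.

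**Stronger consequences are not shown.**
- A reader might infer a renal safety hazard from the 1.3-fold higher exposure reported in Stage 4 impairment. The same part of section 2.2 says that no dosing alteration is needed in renal impairment and that no obvious effect on safety was seen. It also says that there are no data in renal failure.
- A reader might infer that one ineligible patient's event could decide dose escalation, as each cohort has four patients on favipiravir. A DLT must be independently assessed as possibly or probably related (section 9.1.1), and escalation rests on a two-parameter Bayesian model and committee review. No calculation shows that one event would settle the decision.
- A reader might infer bias in the Day 3 comparison. Keeping every randomised patient is ordinary intention-to-treat practice, and no bias follows from that alone.

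**Conclusion.** The contradiction is real and can be verified from the protocol text alone. Footnote d and the section 8.2.1 waiver cannot both apply to LFTs and eGFR alongside exclusion criteria 1 and 2, footnote a and section 5.5. Followed literally, and with same-day screening, footnote d allows a patient whose status on those criteria is unknown to be randomised and dosed, and that patient then enters the analysis populations.

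The size cannot be given, because the documents provide no basis for estimating how many patients would be affected. The conclusion does not depend on a number. It rests on two readings of the text: that footnote d means what it says in the cells where it is printed, and that section 5.2 gives no other source for the values. The master protocol, to which the criteria are also attributed, was not available. If it fixes such a source or ranks the instructions, the candidate-specific protocol still needs to say so.

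The point deserves correction because it concerns a participant-safety check and costs little to put right. It does not show that excluded patients were or will be treated.

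**What to change.** The sponsor should reconcile footnote d of section 1.3 and the baseline bloods bullet in section 8.2.1 with footnote a, section 5.2 and section 5.5, specifically for LFTs and eGFR. The revised text should make clear how criteria 1 and 2 are established when eligibility is confirmed, including when screening and Day 1 coincide. The two placements of the waiver, screening in the schedule and baseline in section 8.2.1, should be aligned so that all sites apply one eligibility rule. How the passages are reconciled is a clinical decision for the sponsor.

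The cost is an edit to one footnote and one bullet. Depending on how the sponsor resolves it, some patients may wait a short time for routine results before randomisation. No design parameter, sample size or analysis changes.
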